## Abstract

**Background/Objectives**: Approximately 30% of women experience pelvic pain one year after vaginal delivery, and this increases to 50% during vaginal intercourse. Multimodal physiotherapy is the first-line treatment for myofascial pain of the pelvic floor muscles (PFM), often incorporating emerging technologies like radiofrequency, despite limited evidence supporting its use. The RASDOP study aims to (i) evaluate the effectiveness of multimodal physiotherapy combining therapeutic education, PFM training, and myofascial pain syndrome (MPS) management with or without radiofrequency, in reducing pain and improving sexual function postpartum; and (ii) explore the barriers and facilitators influencing adherence and perceived self-efficacy towards physiotherapy treatment in women with postpartum pelvic pain. **Methods**: This study employs a randomized clinical trial with a blinded examiner and two parallel groups, followed by a qualitative phenomenological study. A total of 124 postpartum women with pelvic pain (≥4 cm on the visual analogue scale) will be randomized into two groups: a multimodal physiotherapy group (therapeutic education, MPS treatment, and PFM training) and a radiofrequency + multimodal physiotherapy group (same treatment with additional non-ablative radiofrequency). Both groups will receive 12 supervised individual sessions. Assessments will be conducted pre- and post-intervention, and at 3-, 6-, and 12-month stages post-treatment. Primary outcomes include pain intensity and sexual function, while secondary outcomes involve PFM tone, strength, MPS presence, levator ani length, and distress caused by pelvic floor dysfunction. The qualitative study will utilize semi-structured interviews and focus groups analyzed thematically. **Results**: Radiofrequency is expected to enhance pain relief, sexual function, and PFM relaxation. Insights into adherence and barriers will aid in personalizing physiotherapy interventions. **Conclusions**: The RASDOP study will provide evidence on the safety and efficacy of radiofrequency in postpartum pelvic pain treatment and shed light on women’s experiences to improve therapeutic outcomes.

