## 2. Materials and Methods

### 2.1. Study Design

The RASDOP study is a mixed-methods study comprising a single-blind RCT and a qualitative component. The RCT will follow a two-parallel-arm design. Outcome assessment will be blinded, meaning that the evaluators conducting the assessments will not be aware of the participants’ group allocation to reduce detection bias. However, due to the nature of the interventions, neither participants nor treating physiotherapists will be blinded. In parallel, a qualitative study will be conducted using a phenomenological approach, involving individual and group interviews with women from the RCT.

This study has been approved by the Research and Animal Experimentation Ethics Committee of the University of Alcalá under registration number CEIP/2023/3/056. This study has also been registered on the ClinicalTrials.gov platform under the identification code NCT06469632.

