
**Table 1 jcm-14-01489-t001:** Study assessed variables and evaluations.

Assessed Variables	Assessment				
	A0	A1	A2	A3	A4
Sociodemographic variables (address, telephone number, mail, profession, studies, date of birth)	X	only if changes	only if changes	only if changes	only if changes
General clinical data (weight, height, medication, diagnosed pathologies, surgeries, allergies, sports routines, healthy habits)	X	only if changes	only if changes	only if changes	only if changes
Gynecological history (pregnancies, weight gain during pregnancy, type of delivery, presence and degree of tear, presence of episiotomy, weight and length of the baby, breastfeeding, menstruation, symptoms of pelvic floor dysfunction)	X	only if changes	only if changes	only if changes	only if changes
Pelvic floor observation (contraction capacity, relaxation capacity, apnea, parasitic muscle contraction, reflexes, symmetries, perineal scars)	X	X	X	X	X
PFM objective evaluation (Modified Oxford scale, tone and strength by vaginal dynamometry; rest, PFM contraction and bearing down by transperineal ultrasound)	X	X	X	X	X
Diagnosis of MPS (pain: description, intensity, body chart, triggering factor; palpation of abdominal and pelvic floor surface and deep muscles)	X	X	X	X	X
Questionnaires (FSFI, PFDI-20, PFIQ-7, Broome scale)	X	X	X	X	X

A0: pre-treatment assessment, A1: post-treatment assessment, A2: 3-month assessment after treatment, A3: 6-month assessment after treatment, A4: 12-month assessment after treatment, PFM: pelvic floor muscles, MPS: myofascial pain syndrome, FSFI: Female Sexual Function Index, PFDI-20: Pelvic Floor Distress Inventory–short form, PFIQ-7: Pelvic Floor Impact Questionnaire–short form.

**Table 2 jcm-14-01489-t002:** Diagnostic clinical criteria for identifying active and latent myofascial trigger points.

Essential Criteria	Active MTrPs	Latent MTrPs
Palpable taut band	X	X
Exquisite local tenderness upon pressure over a nodule within the taut band	X	X
Patient recognition of their typical pain upon pressure applied to the tender nodule	X	
Painful limitation of the range of motion upon full muscle stretch	X	X

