#### 2.2.5. Intervention

Participants will be randomly assigned in a 1:1 ratio to one of two intervention groups using a computer-generated randomization sequence (Epidat 4.2, Xunta de Galicia, Spain). To ensure allocation concealment, the randomization sequence will be generated in advance by an independent researcher and stored in sealed, opaque, consecutively numbered envelopes. These envelopes will be securely kept and opened only by the designated physiotherapist (PT2) at the time of each participant’s enrollment. PT2 will not be involved in participant assessment or treatment to prevent potential allocation bias. Block randomization with variable block sizes will be used to maintain balance between groups throughout the study.

Participants will be allocated to either the active control group receiving multimodal physiotherapy (MP-G) or the experimental group receiving multimodal physiotherapy including radiofrequency (RMP-G). Both interventions will be individualized and administered by physiotherapists specializing in Pelvic and Women’s Health (PT3 and PT4), who will remain blinded to group allocation to ensure assessor masking. The approximate session duration will be 45 min per session, twice a week for 6 weeks, totaling 12 sessions. Both groups will receive therapeutic education, specific PFMT, and conservative and/or invasive treatment for MPS, with the addition of radiofrequency in the RMP-G. The details of each treatment strategy are explained below.

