
To assess the safety of the interventions, in all treatment sessions, the physiotherapists performing the treatments (PT3 and PT4) will record any potential incidents, such as discomfort, increased pain, use of medication, need for additional medical consultations, postponement, or suspension of treatment due to possible adverse effects of the interventions.

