As a limitation, considering the multifactorial etiology of postpartum pain, hormonal factors may predispose women to greater sexual dysfunction, such as genitourinary syndrome of lactation [60]. To address this, variables related to changes in breastfeeding and the return of menstruation will be collected, as these factors may influence the presence or absence of pelvic pain and sexual function. Additionally, the personal process of role transitions that women experience during this stage of life may play a significant role in sexual dysfunction, beyond purely physical factors [61]. Therefore, another limitation of this study is the absence of a prior neuropsychiatric evaluation. To mitigate this, participants will be asked whether they have previously attended or are currently attending a mental health service. For immediate postpartum perineal pain, the standard medication protocol consists of paracetamol or non-steroidal anti-inflammatory drugs as needed [62,63]. Since medication use will not be altered within the study, any intake by participants will be recorded at each assessment.

If the multimodal physiotherapy treatment that includes radiofrequency is proven to be effective and safe in managing postpartum pelvic pain and sexual function, this conservative therapeutic strategy could be widely implemented to support these women. Furthermore, the qualitative study will provide insights into the factors influencing adherence to healthy habits and home exercises among women experiencing postpartum pain. This knowledge will facilitate the development of treatment programs designed to ensure long-term effectiveness by promoting patient adherence and motivation.

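### Safety is a stated aim, but the described method records incidents only in the treatment sessions, so later adverse events, and those in women who stop early, are not asked about

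*Protocol article*

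**What the plan says.** **Aim.** The Abstract says the study "will provide evidence on the safety and efficacy of radiofrequency in postpartum pelvic pain treatment". Section 3 (Results) gives effectiveness and safety together as what the trial will assess, and section 4 (Discussion) says the design will allow both to be evaluated. The Discussion also has a conditional sentence on implementation: "If the multimodal physiotherapy treatment that includes radiofrequency is proven to be effective and safe", the strategy could be used widely.

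**Method.** Under section 2.2.5, "in all treatment sessions, the physiotherapists performing the treatments (PT3 and PT4) will record any potential incidents". The examples listed are "discomfort, increased pain, use of medication, need for additional medical consultations, postponement, or suspension of treatment due to possible adverse effects of the interventions". Sessions run twice a week for 6 weeks, 12 in all, and radiofrequency starts at the third.

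**Who records.** Section 2.1 states that "due to the nature of the interventions, neither participants nor treating physiotherapists will be blinded". Section 2.2.5 describes the treating physiotherapists as "PT3 and PT4), who will remain blinded to group allocation to ensure assessor masking".

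**After treatment.** Assessments follow at the end of treatment (A1) and 3, 6 and 12 months later (A2 to A4). Table 1 updates "General clinical data (weight, height, medication, diagnosed pathologies, surgeries, allergies, sports routines, healthy habits" if anything has changed. It repeats the pelvic floor observation (including perineal scars), the pain description and the questionnaires every time. The Discussion adds that medication intake is noted at each assessment. The questionnaires are completed online, on a form e-mailed after each assessment (section 2.2.3).

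**The concern.** Section 2.2.5 does more than stay silent on detail. It says how safety will be assessed, and in doing so fixes the occasion (treatment sessions) and the recorder (the therapist giving the treatment). Two gaps follow. A reaction that appears after the last session has no later session at which it can be recorded. A woman who stops treatment early has no further sessions either, and her reasons and later course may be the most informative for safety.

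The recorders also know what they have just applied, and section 3.1 says in advance that no adverse effects are expected in either arm. If few or no incidents are logged, the reader needs to know over what period, and by whom, they were sought, and how much risk the result leaves open.

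**Working it through.** **1. Coverage, from the article's own schedule.**
- Sessions: 12 over 6 weeks. Radiofrequency from session 3 gives up to 12 − 2 = 10 exposures.
- An event between two sessions can be picked up at the next one. An event after session 12, or after a woman's last attended session, cannot.
- A1 to A4 record pain intensity, pelvic floor observation, the FSFI, PFDI-20 and PFIQ-7, medication, and changes in diagnoses or surgery. These are outcomes and background data. None is described as a question about adverse events, and section 2.2.5 does not link them to the safety assessment.

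**2. Blinding.** Section 2.1 says treating physiotherapists are not blinded. Section 2.2.5 says PT3 and PT4 are, and also that they administer both interventions and log the incidents. A therapist who applies the radiofrequency electrodes knows that she did so, so the second statement cannot hold literally for those who treat.

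**3. The stated sample size.** Section 2.2.2 uses FSFI only: difference 2.4, standard deviation 4.5, two-sided alpha 0.05, power 0.8, dropout 10%.
- n = 2 × (1.96 + 0.842)² × 4.5² / 2.4² ≈ 55.2, so 56 per arm.
- 56 × 1.10 = 61.6, so 62; 56 / 0.90 = 62.2, so 63. The stated 62 is reproduced.
- Safety played no part in the sizing.

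**4. What zero events would show.** The exact binomial upper limit for 0 events in n women is 1 − 0.05^(1/n) one-sided and 1 − 0.025^(1/n) two-sided, at 95%.

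| Women observed | One-sided | Two-sided |
|---|---|---|
| 62 (full arm) | 4.7% | 5.8% |
| 56 (after 10% dropout) | 5.2% | 6.4% |

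One event in 62 would give 7.4% one-sided and 8.7% two-sided.

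**5. Chance of seeing at least one event in 62**, 1 − (1 − p)^62, for assumed true risks p (the article gives none):
- p = 1%: 46%
- p = 2%: 1 − 0.29 = 71%
- p = 3%: 1 − 0.15 = 85%

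**The case against.** Several stronger readings are tempting, and the article does not support them.

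- *The trial has decided to declare radiofrequency safe if nothing is recorded.* The sentence in the Discussion begins with a condition and is not a reporting rule; the Abstract promises only evidence. What stands is that the sentence treats proof of safety as something this trial could deliver.
- *Nothing about harm is collected after session 12.* This is wrong. Worsening pain, scar findings, new pelvic floor symptoms, medication and new diagnoses would all leave a trace at A1 to A4, with the examination done by the blinded assessor. The gap is narrower: no adverse-event enquiry is described.
- *Moderately rare harms would probably be missed.* At true risks of 2% to 3% at least one event is more likely than not to be seen, if it occurs when someone is asking. The chance falls below one half only under about 1.1%.
- *62 women cannot exclude a risk of 1 in 20.* That depends on sidedness and dropout: 0 of 62 just excludes 5% one-sided, but not two-sided, and 0 of 56 excludes it on neither.
- *The therapists judge causality.* The closing phrase about possible adverse effects may qualify only postponement or suspension, so this is one reading among two.
- *Recording covers 6 of about 58 weeks (6 + 52), so most of the risk is missed.* Radiofrequency is given only within those 6 weeks, so the share of time is not a share of risk.

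It is also fair to say that limited precision for rare harms affects any trial of this size, and that an article may condense fuller safety procedures. The first point supports only reporting an interval. The second does not remove the gap, because the article states the procedure and its timing itself; if the full protocol also asks at follow-up, section 2.2.5 describes it too narrowly.

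**Conclusion.** The point holds in a limited form. For a stated aim, the described recording stops with the treatment sessions and is done by the people delivering the treatment, whose blinding is described in two incompatible ways. Adverse events arising after the last session, or in women who stop early, are not described as being asked about, although participants are followed for a year.

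On size, the outcome that the article expects, no adverse effects, would leave a risk of up to 5.8% open (two-sided 95%; 4.7% one-sided), or 6.4% (5.2%) with 56 women. These limits assume zero events, that every counted woman was treated, and that every event was sought and recorded. The last assumption is what the present method weakens. The documents do not show how many delayed events would be lost, so no figure is put on that.

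The sample size reproduces and the efficacy comparison is untouched.

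**What to change.** 1. Add a short adverse-event item, worded identically for both arms, to the online form already sent after A1 to A4. PT1 should neither ask it nor see the answers, so that a description of a reaction does not reveal the arm.
2. Send the same item at the same times to women who stop treatment early.
3. Reconcile sections 2.1 and 2.2.5 on the blinding of PT3 and PT4.
4. Report the number of women with any event by arm, with exact 95% confidence intervals, and state who recorded the events and over what period.
5. In the Discussion, replace the reference to proof of safety with an observed rate and its upper limit.

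Cost: one extra form item, one extra table and some rewording. One limit remains: participants know their arm, so self-report does not remove reporting bias. It does make the enquiry the same in both arms and extends it over the full follow-up.

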#### 2.2.6. Statistical Data Analyses

A descriptive analysis of each collected variable will be conducted. For continuous variables, means, medians, standard deviations, and quartiles will be calculated, depending on whether the assumption of normality is met, as determined beforehand using the Shapiro–Wilk test. Qualitative variables will be described with absolute and relative frequencies in percentages.

For intragroup comparisons over time (A0–A4), if continuous variables follow a normal distribution, repeated-measures ANOVA will be used. If the data do not follow a normal distribution, the Friedman test will be used. For ordinal variables (FSFI, PFDI-20, PFIQ-7, Broome Scale), the Friedman test will be used for comparisons across more than two time points, or the Wilcoxon signed-rank test for comparisons between two time points, regardless of whether they follow a normal distribution. For dichotomous variables, the McNemar test will be applied for two time points, and the Cochran Q test will be used for multiple time points.

To determine the association between groups at each time point, a dichotomous independent variable and a quantitative dependent variable with a parametric distribution, the independent Student’s t-test will be used if the data follow a parametric distribution. If the assumption of normality is violated, the Mann–Whitney U test will be applied. For ordinal variables, the Mann–Whitney U test will be used to compare two independent groups, and the Kruskal–Wallis test will be applied for comparisons across more than two groups. For dichotomous variables, the Chi-square test will be used, and Fisher’s exact test will be applied if the expected frequency is less than 5. The effect will be assessed by the difference in means, and the precision will be measured using the 95% confidence interval.

The main analysis to compare the groups will be adjusted to the baseline pre-intervention values of the outcome variables. In all cases, a significant level of *p* < 0.05 will be used. The statistical software SPSS, version 29, IBM, will be employed.

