
The long-term maintenance of positive outcomes depends not only on the treatment but also on behavioral changes and adherence to the physiotherapist’s recommendations [31]. Therefore, exploring and understanding women’s motivation, perceived self-efficacy, and expectations, among other factors, seems essential to ensuring the long-term effectiveness of conservative treatments [32].

The RASDOP study is designed to (i) compare standard multimodal physiotherapy for postpartum pelvic pain with an experimental approach that includes radiofrequency therapy, whose efficacy and safety remain unknown; and (ii) explore factors influencing therapeutic adherence and perceived self-efficacy, identifying the challenges and facilitators that affect postpartum women in adopting and maintaining recommended practices for long-term benefits.

Our hypothesis is that the inclusion of radiofrequency within a multimodal physiotherapy treatment enhances its efficacy in managing postpartum pelvic pain by reducing pain, improving sexual function, eliminating the presence of MPS in the PFM, and improving PFM qualities. Additionally, factors influencing postpartum women’s adherence or non-adherence to a conservative treatment plan for pelvic pain will be explored. These findings will assist clinicians in decision-making regarding the inclusion of technologies such as radiofrequency in the management of pain in this population and provide insights to guide the development of a biopsychosocial approach to postpartum pain treatment.

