#### 2.2.1. Study Participants

Postpartum women experiencing pelvic pain following a vaginal delivery, referred by the Gynecology and Obstetrics Department of Príncipe de Asturias University Hospital for physiotherapy assessment. Physiotherapy assessments and treatments will be conducted at the laboratory of the Physiotherapy in Women’s Health (FPSM) Research Group at the University of Alcalá.

The inclusion criteria will be primiparous women who have had a vaginal delivery, within the past 6 weeks–6 months, experiencing postpartum pelvic pain with an intensity of ≥4 cm on the visual analog scale, and who have read, understood, and freely signed the informed consent. Women will be excluded if they are multiparous, have undergone instrumental vaginal delivery or cesarean section, experienced avulsion of the levator ani muscle, sustained a third- or fourth-degree perineal tear, have a history of pelvic fractures and/or neoplasms, are pregnant, have neurological conditions, an active vaginal or urinary tract infection, an intrauterine device with metallic components, or cognitive, auditory, and/or visual impairments that prevent them from understanding the information, responding to questionnaires, providing consent, and/or participating in the study. Women who have received or are currently undergoing medical or physiotherapeutic treatment for pelvic pain will also be excluded. The enrollment, allocation, treatment, and follow-up scheme for the participants is shown in Figure 1.

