### 3.1. RASDOP Randomized Controlled Clinical Trial Expected Results

The multimodal physiotherapy intervention, based on therapeutic education, PFMT, treatment of MPS in the abdominal and/or PFM, and the use of radiofrequency in women with pelvic pain after childbirth, is expected to significantly improve pelvic floor symptoms in these women. Thus, the RASDOP study is proposed as a solution to improve symptoms related to pelvic pain, the potential occurrence of urinary incontinence, increased urinary frequency, or even the presence of involuntary gas leakage in the postpartum period.

A significant improvement is expected in sexual function, particularly in the domains of lubrication, orgasm, and pain, as assessed by the FSFI questionnaire. Regarding distress and the impact of other pelvic floor dysfunctions, such as lower urinary tract issues, pelvic organ prolapse, and anorectal dysfunctions, evaluated through the PFDI-20 and PFIQ-7 questionnaires, a decrease of more than a 23% in the scores is anticipated, indicating an improvement in symptoms and a reduced impact on quality of life [48].

An increase in the strength of the PFM is expected, as measured by vaginal dynamometry, due to the performance of PFMT and the adoption of healthy PFM protection habits. In contrast, an improvement in the relaxation capacity and elasticity of the PFM is anticipated, as assessed by transperineal ultrasound.

It is expected that the presence of MTrPs in the abdominal muscles and PFM will decrease or even be eliminated. In cases where MTrPs are still palpated, it is anticipated that they will be latent and not trigger painful symptoms in the women.

The Broome scale will be used to assess self-confidence and self-efficacy in performing PFMT, as well as changes in lifestyle behavior, which are expected to help sustain treatment benefits in the long term. It is anticipated that participants in both groups will achieve a score of over 66 points on the Broome scale during the post-treatment and follow-up evaluations, indicating a high perception of self-efficacy [46].

Although both intervention groups are expected to show significant improvements between the pre- and post-treatment assessments, and maintain their results at 3-, 6- and 12-month stages post-treatment, it is anticipated that these improvements will be greater in all variables in the RMP-G group, particularly in sexual function, pain reduction, and the lower presence of MTrPs.

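### With multimodal physiotherapy in both arms, the trial identifies only the effect of adding radiofrequency; aim (i) and the expected results reach for the whole package, on which only uncontrolled within-arm tests bear

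*Protocol article*

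**What the plan says.** - **Arms (2.2.5).** "Both groups will receive therapeutic education, specific PFMT, and conservative and/or invasive treatment for MPS, with the addition of radiofrequency in the RMP-G". There is no untreated, sham or waiting-list arm.
- **Aim in the Abstract.** Aim (i) is to "evaluate the effectiveness of multimodal physiotherapy combining therapeutic education, PFM training, and myofascial pain syndrome (MPS) management with or without radiofrequency".
- **Aim in the Introduction.** The trial is to "compare standard multimodal physiotherapy for postpartum pelvic pain with an experimental approach that includes radiofrequency therapy". The Conclusions likewise ask whether including radiofrequency enhances the treatment.
- **Within-arm analysis (2.2.6).** "For intragroup comparisons over time (A0–A4), if continuous variables follow a normal distribution, repeated-measures ANOVA will be used". Friedman is the non-normal alternative, and Friedman or Wilcoxon tests serve the questionnaires. One significance level, p < 0.05, applies throughout. These analyses are not labelled descriptive.
- **Between-arm analysis (2.2.6).** "The main analysis to compare the groups will be adjusted to the baseline pre-intervention values of the outcome variables". The effect is to be given as a difference in means with a 95% confidence interval.
- **Expected results (3.1).** "both intervention groups are expected to show significant improvements between the pre- and post-treatment assessments". The same sentence then predicts a larger improvement in the radiofrequency arm.
- **Section 4, closing paragraph.** It looks ahead to wide use if the multimodal treatment that includes radiofrequency is shown to be effective and safe.
- **Entry (2.2.1).** Women "experiencing postpartum pelvic pain with an intensity of ≥4 cm on the visual analog scale", with a delivery "within the past 6 weeks–6 months".

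**The concern.** Radiofrequency is the only thing that differs by randomisation. Whether the package of education, muscle training and myofascial treatment works has no concurrent comparator in this trial. A reader who takes aim (i) and section 3.1 at face value will look for an answer to that question, and the only planned analyses that speak to it are the within-arm tests.

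Those tests ask whether the mean changed over time, not why. Women enter within six months of delivery and are followed to 12 months after treatment. Section 4 itself says that changes in breastfeeding and the return of menstruation may influence pain and sexual function. Pain is also a primary outcome with an entry threshold, so selection can produce an apparent fall. At stake is a published statement that multimodal physiotherapy is effective, resting on a test that can be significant with no treatment effect.

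**Working it through.** **1. The plan's own figure.** Section 2.2.2 gives a difference of 2.4 FSFI points, SD 4.5, two-sided alpha 0.05, power above 0.8 and 10% dropout.

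n = 2 × [4.5 × (1.960 + 0.842) / 2.4]² = 55.2, so 56 per arm. 55.2 / 0.9 = 61.3, so 62 per arm.

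The stated 62 reproduces. It is a between-arm calculation, consistent with the comparative aim. I use 56 completers per arm below.

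**2. Inputs for the illustration.** The 40 mm threshold is from 2.2.1. The article gives no VAS mean, SD or test–retest correlation, so these are assumptions: source mean μ = 40–50 mm, σ = 20 mm, ρ = 0.7–0.9, normal readings, no treatment effect and no recovery.

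**3. Case A: the A0 reading is the one that met the threshold.**

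- With a = (40 − μ)/σ and λ = φ(a)/[1 − Φ(a)], mean A0 = μ + σλ.
- Expected fall from A0 to A1 = (1 − ρ)σλ.
- Variance of the change = (1 − ρ)²σ²(1 + aλ − λ²) + σ²(1 − ρ²).
- Probability of significance comes from the non-central t distribution, two-sided, 55 degrees of freedom.

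For μ = 40 and ρ = 0.7: λ = 0.798, the fall is 0.3 × 20 × 0.798 = 4.8 mm, and the SD of change is 14.7 mm. Non-centrality is 4.79 / (14.73/√56) = 2.43, giving probability 0.67.

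| μ (mm) | ρ | Fall (mm) | SD of change (mm) | P(p < 0.05), paired test | P(p < 0.05), repeated-measures ANOVA A0–A4 |
|---|---|---|---|---|---|
| 40 | 0.7 | 4.8 | 14.7 | 0.67 | 0.66 |
| 40 | 0.9 | 1.6 | 8.8 | 0.27 | 0.23 |
| 50 | 0.7 | 3.1 | 14.9 | 0.33 | 0.29 |
| 50 | 0.9 | 1.0 | 8.8 | 0.14 | 0.11 |

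The last column is simulated (5,000 trials per row, equal correlation between all visits) because 2.2.6 plans repeated-measures ANOVA for a normal continuous outcome. The two tests agree closely. If 5 mm of natural recovery is added, the paired test is significant with probability 0.98 or more in every row.

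**4. Case B: eligibility used a separate, earlier reading.** Under the same model A0 and A1 have the same expectation, so regression to the mean between them is zero and the probability is the nominal 0.05. With 5 mm of recovery, SD of change = 20√[2(1 − ρ)] = 15.5 mm (ρ = 0.7) or 8.9 mm (ρ = 0.9), and the probability is 0.66 or 0.98.

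**5. Against the article's own yardstick.** Section 2.2.3 takes 15 mm as the change required for clinical significance on VAS. The falls of 1.0–4.8 mm are far below it, but 2.2.6 does not tie the within-arm tests to that threshold.

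**6. The randomised contrast.** Recovery and regression to the mean have the same expectation in both arms and cancel in the between-group difference.

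**The case against.** The strongest reply is that the plan is already comparative where it counts. The Introduction, the hypothesis, the opening of sections 3 and 4 and the Conclusions all ask what radiofrequency adds. Section 2.2.5 calls multimodal physiotherapy the active control. Section 2.2.6 names a baseline-adjusted comparison as the main analysis, and the sample size is for a between-arm difference. The phrase in aim (i) can be read as naming the two arms. All of this stands, and it makes the point one of wording.

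Two stronger readings are tempting. A reader might infer that the plan will present within-arm significance as proof of efficacy. No section states such a rule; 3.1 is a narrative of expectations, and its sentence ends on the between-arm contrast. A reader might also infer that significance in one arm but not the other will be taken as a treatment difference. Nothing in the article proposes that, and direct between-group tests are planned at each time point.

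The figures are also open to challenge. Every VAS input apart from the threshold is assumed, the article does not say whether A0 is the qualifying reading, and section 4 notes that untreated pain can persist, so the amount of recovery is unknown. That stands too, which is why both cases are shown.

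What the reply does not remove is that aim (i), 3.1 and the end of section 4 can be read as claims about the whole package, while the only analyses bearing on them are uncontrolled tests at p < 0.05 not marked as descriptive.

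**Conclusion.** The point holds as a mismatch between part of the stated aim and what the design can identify. The trial can estimate the effect of adding radiofrequency; it cannot show that multimodal physiotherapy, with or without radiofrequency, is effective.

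With no treatment effect and no recovery, a within-arm VAS test would be significant with probability about 0.1–0.7 if A0 is the qualifying reading, and 0.05 if it is not. This range rests wholly on the assumed mean, SD and correlation and is an illustration, not an estimate for this population. The threshold acts directly on pain; for FSFI the concern is mainly natural recovery. The claim that a within-arm test cannot separate treatment from recovery needs none of these figures. The randomised comparison is sound on this point.

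**What to change.** 1. Abstract aim (i), section 3.1 and the closing paragraph of section 4: align with the Introduction and Conclusions, so that the aim and the expected results concern the effect of adding radiofrequency to multimodal physiotherapy.
2. Section 2.2.6: label the intragroup analyses as descriptive and report them as change from A0 with a 95% confidence interval.
3. Section 2.2.6: state that efficacy conclusions rest only on the randomised, baseline-adjusted between-group difference.

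The cost is a few sentences. Data collection, sample size and treatment do not change. The downside is giving up a claim about the package as a whole, which this design cannot support.
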